### 6.2.3 Unblinding

Adherence to blinding will be rigorously maintained by concealing the perfusion chart, containing the treatment allocation and details of its delivery. At sites with a paper perfusion chart, this will be placed in a sealed envelope within the medical notes *before* leaving theatre. At sites with an electronic perfusion chart, access to the data will be restricted to prevent inadvertent unblinding and views will be automatically logged. Allocation to the treatment will not be recorded in patient's electronic medical records. In the unlikely event of an emergency in which knowledge of the allocation may affect patient care or other safety reasons, the sealed envelope may be opened. Any member of staff accessing these documents will be required to record their name, sign, date/time, and the reason for opening the envelope, and each site will be monitored. At patient handover to PICU following surgery, information on the type, dosing, and timing of the cardioplegia will not be provided to the receiving team.

### 6.2.4 Randomisation Process

After participant eligibility has been confirmed and informed consent has been received, the participant can be randomised into the trial. Randomisation Notepads will be provided to investigators and will be used to collate the necessary information prior to randomisation. All questions and data items on the Randomisation Notepad must be answered before a Trial Number can be given. If data items are missing, randomisation will cease and must be re-started anew once the information is available.

Randomisation will be provided by a secure online randomisation system at the Birmingham Clinical Trials Unit (BCTU) (available at <https://www.trials.bham.ac.uk/DESTINY>). Unique log-in usernames and passwords will be provided to those authorised to use the online system and who have been delegated the role of randomising participants into the study as detailed on the **DESTINY Site Signature and Delegation Log**. These unique log-in details must not be shared with other staff and in no circumstances should staff at sites access either the randomisation process or trial database using another person's login details. The online randomisation system will be available 24 hours a day, 7 days a week, apart from short periods of scheduled maintenance

### 6.2.5 Randomisation Records

Following randomisation, a confirmatory e-mail will be sent to the randomiser (usually research nurse or perfusionist), DESTINY Trial Manager and CI.

Investigators will keep their own study file log which links participants with their allocated trial number in the **DESTINY Participant Recruitment and Identification Log**. The Investigator must maintain this document, which is **not** for submission to the Trials Office. The Investigator will also maintain the **DESTINY Participant Screening and Enrolment Log** which will be housed electronically on the REDCap database. The **DESTINY Participant Recruitment and Identification Log** and **DESTINY Participant Screening and Enrolment Log** should be held in strict confidence.

### 6.2.6 Informing Other Parties

The participant's General Practitioner will be notified that they are taking part in the trial using the **DESTINY GP Letter**. Allocation to the trial treatment will not be disclosed to GP. No other parties will be specifically informed of participation.

## 7 TRIAL TREATMENT / INTERVENTION

### 7.1 Intervention(s) and Schedule

The trial interventions are either del Nido cardioplegia (experimental arm) or St. Thomas' blood cardioplegia (control arm). The two cardioplegia solutions are compared in **Table 1**.

| del Nido cardioplegia                                                 | St. Thomas' blood cardioplegia (Harefield preparation) |
|-----------------------------------------------------------------------|--------------------------------------------------------|
| 1 litre Plasma-Lyte A base solution to which the following are added: |                                                        |
| Mannitol 20%, 16.3ml                                                  | Sodium chloride 8.6g                                   |
| Magnesium sulfate 50%, 4ml                                            | Magnesium chloride 6.262g                              |
| Sodium bicarbonate 8.4%, 13ml                                         | Calcium chloride 330mg                                 |
| Potassium chloride 2mEq/ml, 13ml                                      | Potassium chloride 6.252g                              |
| Lidocaine 1%, 13ml                                                    | Procaine hydrochloride 1364mg                          |
| Total volume: 1052.8ml                                                | In water for injection, per 1000ml                     |

**Table 1.** Table comparing the crystalloid components of the experimental (del Nido) and control (St. Thomas') treatments [42].

The del Nido and St. Thomas' blood cardioplegia also differ in their formulations and doses as depicted in **Table 2**.

| Arm          | IMPs                          | Formulations                                               | Dose                                                                                                           |
|--------------|-------------------------------|------------------------------------------------------------|----------------------------------------------------------------------------------------------------------------|
| Experimental | del Nido cardioplegia         | 1:4 blood:crystalloid preparation                          | Initial dose of 20ml/kg and subsequent doses every 60-90 minutes if required, at the discretion of the surgeon |
| Control      | St Thomas' blood cardioplegia | 4:1 blood:crystalloid using Harefield Hospital preparation | Initial dose of 20-30ml/kg, subsequent doses of 15 ml/kg every 20-30 minutes, at the discretion of the surgeon |

**Table 2.** Acceptable formulations of IMP and dosage of experimental vs control arm.

The allocated cardioplegia solution will be administered according to the above preparation and schedule by the Clinical Perfusionist, at the request of the operating surgeon, in an antegrade manner via an aortic root or direct coronary ostia canula, following placement of a cross-clamp on the proximal aorta. The glass bottle containing the IMP should be vented using a spike vent or similar during infusion. By placing a waste sucker into the right atrium after commencing its delivery, the systemic bioavailability of the cardioplegia constituents following passage through the coronary circulation will be markedly reduced.

## 7.2 Drug Interaction or Contraindications

Other than the use of an alternative cardioplegia solution for the index operation, there are no restrictions on permitted, prohibited or concomitant medications in this trial. The exclusion criteria include known hypersensitivity or allergy to lidocaine (del Nido cardioplegia) or procaine (St. Thomas' blood cardioplegia).

## 7.3 Treatment Modification

In patients who require repeat aortic cross-clamping during the index procedure (predicted to be <5%), the same cardioplegia solution should be used, if required, but the dose given will be at the discretion of the operating surgeon, i.e. a smaller dose may be considered for an anticipated short period of repeat cross-clamping and recorded in the Perfusion CRF.

In those who require an unplanned reoperation or planned procedure requiring cardioplegia within 30 days of the index procedure, the standard cardioplegia for the centre should be used rather than the IMP. Additional use of cardioplegia during an unplanned procedure within the follow-up period should be recorded in the **Unplanned Reoperation/Intervention CRF**.

## 7.4 Cessation of Treatment / Continuation after the Trial

Cardioplegia is only given during planned surgical ischaemia and therefore the trial treatment will cease once the aortic cross-clamp is removed during the index procedure; if more than one aortic cross-clamping is required, this will be when it is removed for the final time.

## 7.5 Treatment Supply and Storage

### 7.5.1 Treatment Supplies

Both del Nido and St Thomas' cardioplegia will be manufactured and distributed by Stockport Pharmaceuticals, an NHS pharmaceutical manufacturer specialising in sterile IMPs for clinical trials (MIA(IMP) 13523). Drug distribution will be via suitable temperature-controlled processes.

On receipt of a batch of either cardioplegia solution, the NHS recipient must carry out routine checks to ensure that the drug has arrived in a way that is consistent with its despatch i.e. no visible particulate matter, discolouration, leakage, or evidence of temperature deviation. Where any issues are identified, such stock should be quarantined until guidance from the DESTINY Trial Office is received as to whether drug can be used or should be returned to the supplier.

### 7.5.2 Packaging and Labelling

Stockport Pharmaceuticals will package and label the IMPs in accordance with Annex 13 of the Clinical Trials Directive and as per the MHRA approved template, as below:

| For Clinical Trial Use Only                                                                                                                                                                                                                                                                                                                                  |  | 500mL                                                                                                                                                                                                                                                |
|--------------------------------------------------------------------------------------------------------------------------------------------------------------------------------------------------------------------------------------------------------------------------------------------------------------------------------------------------------------|--|------------------------------------------------------------------------------------------------------------------------------------------------------------------------------------------------------------------------------------------------------|
| DESTINY TRIAL
del Nido Cardioplegia
EudraCT number: 2021-001915-10
Instruction for use:
Gently agitate the solution and carefully inspect the contents of the bottle to check that the solution is clear before use. If crystals are present, continue to gently agitate the solution until all crystals have re-dissolved. |  | STOCKPORT PHARMACEUTICALS,
STEPPING HILL HOSPITAL,
[name],
MANMP113323
Sponsor: University of Birmingham, [name]
[contact]
Chief Investigator: [name], contact number: [name] |
| Patient Trial ID:
Batch Number: Vvvvvvvv
Expiry Date: Vvvvvvvv                                                                                                                                                                                                                                                                                         |  |                                                                                                                                                                                                                                                      |
| Store between 2 - 8°C.
Use once only and discard remainder
Keep out of the reach and sight of children                                                                                                                                                                                                                                                 |  |                                                                                                                                                                                                                                                      |
| CTL196B                                                                                                                                                                                                                                                                                                                                                      |  |                                                                                                                                                                                                                                                      |

  

| For Clinical Trial Use Only                                                                                                                                     |  | 500mL                                                                                                                                                                                                                                                |
|-----------------------------------------------------------------------------------------------------------------------------------------------------------------|--|------------------------------------------------------------------------------------------------------------------------------------------------------------------------------------------------------------------------------------------------------|
| DESTINY TRIAL
St. Thomas' Cardioplegia
(Harefield preparation)
EudraCT number: 2021-001915-10
Use as directed in the protocol. |  | STOCKPORT PHARMACEUTICALS,
STEPPING HILL HOSPITAL,
[name],
MANMP113323
Sponsor: University of Birmingham, [name]
[contact]
Chief Investigator: [name], contact number: [name] |
| Patient Trial ID:
Batch Number: Vvvvvvvv
Expiry Date: Vvvvvvvv                                                                                            |  |                                                                                                                                                                                                                                                      |
| Store between 2 - 8°C.
Use once only and discard remainder
Keep out of the reach and sight of children                                                    |  |                                                                                                                                                                                                                                                      |
| CTL197B                                                                                                                                                         |  |                                                                                                                                                                                                                                                      |

### 7.5.3 Drug Storage

Upon arrival at site pharmacy from Stockport Pharmaceuticals, the cardioplegia solutions will be stored in a suitable fridge with temperature monitoring capabilities at 2-8°C and segregated from routine clinical stock. Any temperature deviations should be reported to the DESTINY Trial Office using the [DESTINY Temperature Deviation Log](#) immediately upon becoming aware and stock should be quarantined until further guidance becomes available.

Batches of the cardioplegia will be despatched from the hospital pharmacy to the operating theatre for further storage in a new, dedicated, temperature-monitored refrigerator at 2-8°C and in the original packaging, segregated from routine clinical stock with access restricted to perfusion staff only.

## 7.6 Accountability and Compliance Procedures

### 7.6.1 Compliance

The drug is administered by the perfusionist during the index surgery according to unit practice and compliance can therefore be verified by the Perfusion CRF.

### 7.6.2 Accountability

Responsible site pharmacy personnel must maintain accurate accountability records of both cardioplegia solutions, including, but not limited to, the number of bottles received, the number of bottles transferred to theatres, batch number, expiry date, and date of transfer. The batch number of each bottle administered will be recorded on the Perfusion CRF. Used bottles of both cardioplegia solutions should be disposed of according to normal local procedures.

**DESTINY Accountability Logs** will be provided by the DESTINY Trial Office for the site pharmacy and theatres to log receipt of batches containing individual bottles of cardioplegia. "Use" includes disposal or destruction of bottles of cardioplegia that have expired or not been used for any reason, including breakage, discolouration, particulate matter, or temperature deviation. Disposal and destruction should be achieved using local protocols.

## 8 OUTCOME MEASURES AND STUDY PROCEDURES

### 8.1 Primary Outcome Measure

Area under the time-concentration curve (AUC) for plasma high-sensitivity troponin-I ( $\mu\text{g.h/L}$ ) in the first 24 hours after the index aortic cross-clamp release (reperfusion).

### 8.2 Secondary Outcome Measures

- Low cardiac output syndrome (LCOS) defined as either of the following in the first 48 hours after reperfusion: Vasoactive Inotrope Score (VIS)  $\geq 15$  [1,2], or major cardiac event (cardiac arrest, ECLS or death) (n) [3]
- Duration of mechanical ventilation (hours), defined as the number of hours from termination of index CPB to extubation
- Length of postoperative stay on Paediatric Intensive Care (hours), defined as number of hours from admission to PICU from theatre following index procedure to discharge from PICU
- Maximum VIS by thresholds:  $\geq 10$ ,  $\geq 15$  and  $\geq 20$  in the first 48 hours (n)
- Total VIS in the first 4 hours after PICU admission following the index procedure (score)
- Arterial lactate (mmol/L) in the first 12 hours
- *Omega*, determined by  $[\text{SaO}_2]/[\text{SaO}_2 - \text{ScvO}_2]$  in the first 12 hours [4]
- Total aortic cross-clamp time (mins)
- Total volume of cardioplegia given (ml)
- Need for internal defibrillation during reperfusion (n)
- Delayed sternal closure, incidence (n) and duration (days)
- Unplanned reoperation, including chest re-opening on PICU (n)
- Need for new renal replacement therapy (n)
- Lowest estimated glomerular filtration rate (eGFR), calculated using the bedside Schwartz equation and the peak postoperative creatinine on routine monitoring during the first 7 days following the index procedure ( $\text{ml/min/1.73m}^2$ ), and according to the paediatric RIFLE categories (n) [5]
- Length of postoperative stay in the hospital (days), defined as number of days from day of surgery to discharge from hospital or death, whichever is sooner
- 30-day survival (n)

Detailed information on postoperative healthcare resource use will be collected on all patients from the Paediatric Critical Care Minimum Data Set (PCCMDS) [43], via the Paediatric Intensive Care Audit Network (PICANet), to which all centres routinely contribute. This dataset will be compared with data collected on the trial CRFs to assess the feasibility of using routinely collected outcome data in a trial setting and to inform planning of cost-effectiveness analyses in future trials.

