### 1.1.2 Assessment of myocardial protection

Low cardiac output syndrome (LCOS) in the early postoperative period reflects the degree of myocardial injury and the need for inotropic support to maintain adequate tissue perfusion. The presence of LCOS is a major determinant of outcome after heart surgery in children and most deaths in the early postoperative period are attributed to a low cardiac output [19,20]. However, there are no widely accepted methods for directly measuring cardiac output in young children and therefore the determination of low cardiac output is dependent upon other clinical measures such as need for inotropic support.

Postoperative elevation of plasma troponin is a marker of myocardial injury and has been shown to strongly correlate with clinical outcomes including inotropic support, duration of ventilation, ventricular dysfunction and early death [9,21] consequently, it is the most common

primary outcome measure in clinical trials of myocardial protection in children [22]. Whilst the rise in troponin is strongly correlated with duration of ischaemia [23], it may be further elevated by the surgical intervention, such as ventricular incision or muscle resection [24].

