### **1.1.7 Justification for participant population**

The inclusion criteria are deliberately wide to ensure the generalisability of results. In the absence of more precise data concerning the effects of cardioplegia on the young heart, the commonly accepted societal definition of a child, <16 years of age, has been applied.

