## 2 AIMS AND OBJECTIVES

### 2.1 Main Trial Objectives

#### 2.1.1 Clinical Aims and Objectives

To evaluate whether in children undergoing cardiac surgery with cardioplegic arrest, the use of del Nido cardioplegia, compared with St. Thomas' blood cardioplegia:

- reduces myocardial injury, as determined by AUC for plasma troponin following surgery
- reduces the duration of ischaemia (aortic cross-clamp time), the volume of cardioplegia given, and the need for internal defibrillation during reperfusion
- improves myocardial protection, reducing the frequency or severity of LCOS, and markers of reduced tissue perfusion (arterial lactate and *omega*)
- improves other clinical outcomes, including duration of mechanical ventilation, length of stay on the Paediatric Intensive Care Unit and in hospital, and 30-day survival

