### 4.2 Exclusion Criteria

- Predicted cross-clamp time <30 minutes (e.g. atrial septal defect, atrial septectomy, sub-aortic stenosis) at the discretion of the Consultant surgeon
- Known contraindication to one of the constituents of either cardioplegia solution (e.g. lidocaine/procaine hypersensitivity/allergy) or its method of delivery, including temperature (e.g. haemoglobinopathy including sickle cell disease, cold agglutinins)
- Weight at the time of screening >50kg
- Ventricular assist device (VAD) insertion/explant or transplantation
- Preoperative inotropic support or extra-corporeal life support (ECLS)
- Previous cardiac surgery with cardioplegic arrest within the last 30 days
- Previous enrolment in the DESTINY trial
- Emergency surgery
- Parent/guardian declines consent

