### 6.2 Randomisation

#### 6.2.1 Randomisation Methodology

Participants will be randomised by computer at the level of the individual in a 1:1 ratio to either del Nido cardioplegia or St. Thomas' blood cardioplegia.

A minimisation algorithm will be used within the online randomisation system to ensure balance in the treatment allocation over the following variables:

- Age: neonate (0-30 days), infant (31 days<1 year), child (1<7 years), older child (7<16 years)
- Incision or resection of ventricular myocardium anticipated (yes/no)
- Surgical centre

A 'random element' will be included in the minimisation algorithm, so that each participant has a probability (unspecified here), of being randomised to the opposite treatment that they would have otherwise received.

Full details of the randomisation specification will be stored in a confidential document at BCTU.

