### 13.2 Analysis of Outcome Measures

A separate Statistical Analysis Plan will be produced and will provide a more comprehensive description of the planned statistical analyses. A brief outline of these analyses is given below. The primary comparison groups will be composed of those treated with del Nido cardioplegia versus those treated with St. Thomas' blood cardioplegia. In the first instance, all analyses will be based on the intention to treat principle, i.e. all participants will be analysed in the treatment group to which they were randomised irrespective of compliance or other protocol deviation. For all outcome measures, appropriate summary statistics will be presented by group (e.g. proportions/percentages, mean/standard deviation, or median/interquartile range).

Intervention effects will be adjusted for the minimisation variables listed in section 6.2.1 where possible. No adjustment for multiple comparisons will be made.

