### 13.2.2 Secondary Outcome Measures

Continuous data items will be analysed using a linear regression model. Results will be presented as adjusted mean difference and 95% confidence intervals.

Continuous outcomes measured across more than 3 time points (e.g. arterial lactate and omega) will be analysed as repeated measures using linear mixed models using all available data. Baseline value of the measure (if available) and time by treatment interaction will be included with time as a continuous variable. Results will be presented as mean difference and 95% confidence intervals.

Time-to-event data outcomes (such as time from admission to PICU to discharge from PICU) will be analysed using the Cox regression model. Results will be presented as Hazard ratio and 95% confidence intervals. Kaplan Meier plots will also be presented with the log-rank test for visual interpretation.

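### Total cross-clamp time is compared across a wide mix of operations without the planned operation as a covariate, so this secondary comparison is valid but less precise than it could cheaply be

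*Protocol*

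**What the plan says.** Protocol section 8.2 lists "Total aortic cross-clamp time (mins" among the secondary outcomes. It answers a named aim in section 2.1.1, whether del Nido "reduces the duration of ischaemia (aortic cross-clamp time), the volume of cardioplegia given, and the need for internal defibrillation during reperfusion". Section 1.1.9 presents the longer dosing interval, and the shorter clamp time expected from it, as a specific practical advantage of del Nido.

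On the model, section 13.2.2 says "Continuous data items will be analysed using a linear regression model", reported as an adjusted mean difference with a 95% confidence interval. Section 13.2 names the adjustment: "Intervention effects will be adjusted for the minimisation variables listed in section 6.2.1 where possible". Section 6.2.1 lists three such variables: age in four bands, surgical centre, and "Incision or resection of ventricular myocardium anticipated (yes/no".

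On case mix, section 1.1.7 says "The inclusion criteria are deliberately wide to ensure the generalisability of results". Clamp time limits entry only from below. Section 4.2 excludes "Predicted cross-clamp time <30 minutes (e.g. atrial septal defect, atrial septectomy, sub-aortic stenosis) at the discretion of the Consultant surgeon", and there is no upper limit.

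The baseline assessments before randomisation in section 6.1 do not name the planned operation. Section 13.2 describes itself as an outline and leaves fuller detail to a separate SAP.

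**The concern.** Operations on children differ in how long the aorta must stay clamped, and the protocol relies on this when it gives three procedures as examples of short predicted clamp time. In the stated model, the only term specific to the operation is the yes/no item on ventricular incision or resection. Two children in the same age band and centre with the same answer to that item are treated as having the same expected clamp time, however different their planned repairs. The remaining variation between operations goes into the error term and widens the interval for the treatment difference.

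The information needed is available before allocation. Children are identified from the multidisciplinary meeting, waiting list, clinic or ward (section 3.1.2). The surgeon must judge predicted clamp time against 30 minutes. The ventricular incision item must also be answered before a trial number is issued (sections 6.2.1 and 6.2.4), so the surgical plan is known by then.

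At stake is how clearly the trial can answer its ischaemia objective. A modest real saving in clamp time could be left with an interval too wide to interpret.

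**Working it through.** **Check on the protocol's own figure.** The protocol gives no calculation for clamp time, so the primary-outcome calculation in section 13.1 supplies the group size. Inputs: difference 19.2 µg.h/L, SD 42.0 µg.h/L, type I error 0.05 (taken as two-sided), power 90%, allocation 1:1. The standardised difference is 19.2/42.0 = 0.457. The exact two-sample t-test needs 101.5 per group, so 102 per group and 204 in total. The stated figure reproduces. I use n = 102 per group below.

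**Effect of one more baseline covariate.** Let R² be the share of clamp-time variance explained by the planned operation beyond the three stated covariates.

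- Standard error and interval width are multiplied by √(1 − R²).
- The equivalent increase in sample size is 1/(1 − R²).
- The detectable difference in SD units is (1.960 + z) × √(2/102), times √(1 − R²), with z = 0.842 for 80% power and 1.282 for 90%.

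R² is not in the documents. The range below is assumed.

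| Extra R² (assumed) | Interval width × | Narrowing | Sample multiplier | Detectable at 80% | Detectable at 90% |
|---|---|---|---|---|---|
| 0 | 1.00 | 0% | 1.00 | 0.39 SD | 0.45 SD |
| 0.10 | 0.95 | 5% | 1.11 | 0.37 SD | 0.43 SD |
| 0.30 | 0.84 | 16% | 1.43 | 0.33 SD | 0.38 SD |
| 0.50 | 0.71 | 29% | 2.00 | 0.28 SD | 0.32 SD |

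**Illustration in minutes.** This needs a further assumption: an SD of 30 or 40 minutes, taken as what remains after the three stated covariates. The half-width is 1.96 × SD × √(1 − R²) × √(2/102). Power is Φ(difference / [SD × √(1 − R²) × √(2/102)] − 1.96).

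| SD (assumed) | Extra R² | Half-width (min) | Power, 5 min | Power, 10 min |
|---|---|---|---|---|
| 30 | 0 | 8.23 | 22% | 66% |
| 30 | 0.10 | 7.81 | 24% | 71% |
| 30 | 0.30 | 6.89 | 30% | 81% |
| 30 | 0.50 | 5.82 | 39% | 92% |
| 40 | 0 | 10.98 | 14% | 43% |
| 40 | 0.10 | 10.41 | 15% | 47% |
| 40 | 0.30 | 9.19 | 19% | 57% |
| 40 | 0.50 | 7.76 | 24% | 71% |

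**Cost in degrees of freedom.** Each extra model term uses one degree of freedom out of about 204, roughly 1/204 = 0.5%. A few categories therefore cost little, and a covariate that explained almost nothing would do little harm.

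**Direction.** The planned operation is fixed before allocation, so adjusting for it cannot remove any part of the treatment effect on clamp time.

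**The case against.** The strongest reply is that nothing here is invalid. Linear regression adjusted for the minimisation factors is a standard analysis, and randomisation keeps the comparison unbiased. The outcome is one of sixteen listed secondary outcomes and has no power target. One of the stated covariates is already a feature of the planned operation. Section 13.2 does not say that its list is exhaustive, so the SAP could add a covariate. All of this stands, and it limits the point to precision. What remains is that the protocol names an adjustment set, and that set leaves out a predictor its own exclusion criterion relies on.

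It is also fair to say that the gain is assumed. The formulas only convert an R² into a width, and the documents supply no R².

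A reader might be tempted by three stronger readings, none of which the documents support.

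- *That the primary AUC should be adjusted in the same way.* Section 1.1.2 says "the rise in troponin is strongly correlated with duration of ischaemia", but that concerns the actual duration, which section 1.1.9 expects treatment to shorten. It does not show that the planned operation predicts troponin release beyond the covariates already used. Changing the primary adjustment set while interim primary-outcome data are planned for the DMC (sections 8.3 and 13.3) would also be open to challenge.
- *That a predicted clamp time in minutes is available and goes unused.* Section 4.2 requires only a judgement against 30 minutes. No prediction in minutes is shown to exist. If it were collected from now on, it would exist only for children randomised later, and using minutes for some children and operation groups for others does not define a single model.
- *That the planned operation goes unrecorded.* Its absence from the short list in section 6.1 does not prove this, because section 10.2 names Randomisation and Operation CRFs whose fields are not shown.

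**Conclusion.** The point holds as a matter of precision on one secondary outcome. The stated adjustment for total cross-clamp time omits the planned operation, although entry is wide, the operation is known before allocation, and the protocol itself connects type of operation with predicted clamp time. The estimate is unbiased, but its interval is probably wider than it need be.

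The size cannot be fixed from the documents. Under assumed extra explained variance of 10%, 30% or 50%, the interval narrows by about 5%, 16% or 29%. The figures in minutes rest on a further assumed SD of 30 to 40 minutes and a difference of 5 to 10 minutes. The conclusion also assumes that the SAP has not already added the planned operation; if it has, the point is met. This is a cheap improvement, and neither the validity of the trial nor its primary analysis is in question.

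**What to change.** For the analysis of total cross-clamp time only, add the planned operation to the linear model beside the minimisation variables, for every child.

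- Use the operation as planned and recorded before randomisation, not the operation as performed. The surgeon is unblinded (section 6.2.2), so later records could be influenced by allocation.
- Group operations into a small number of categories, and fix the grouping before treatment codes are joined to the data.
- Confirm that a pre-randomisation record of the planned operation exists for all children. If no CRF holds it, take it from the preoperative healthcare record used to identify patients (section 3.1.2).
- Leave the primary AUC adjustment set unchanged.
- Do not combine predicted minutes for some children with operation groups for others.

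The change is one sentence in section 13.2.2 or the SAP. The cost is the work of classifying the operations, possibly some retrieval from records, and a few degrees of freedom. Categories that overlap heavily with age band or the ventricular incision item will add less, which is another reason to keep them few.
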